### Dissemination policy

Our findings may have important implications for the public health and could potentially enlighten the research community on refining the standard clinical treatment for IXT. All experience summary and results in the research process of this trial will be shared through academic exchange activities, including presentations at relevant scholarly conferences, continued education training course. The final results will be published in peer-reviewed scientific journals. All those who have contributed to the design and conduction will be eligible for authorship of subsequent publications.

## Discussion

The success rate following IXT surgery has been quite variable across studies, which can be attributed to differences in examination methods, criteria for surgical failure, and length of follow-up [8, 21, 29, 30]. It has been confirmed that there is a high rate of exodrift or recurrence after surgery in IXTs. A previous study has indicated that orthoptic therapy is effective in the treatment of convergence insufficiency IXT with a maximum deviation of 25 PD [17, 18]. It has also been applied as a component of a postoperative combination therapy [21] but in a retrospective small sample study. Therefore, there are still many related unanswered questions, such as which patients will respond to this therapy, how long, and at what frequency does orthoptic therapy have to be performed for maximal efficacy, what is the endpoint of treatment and what is the long-term stability of these results. With our study, we hope to answer several of these questions.

One-month post-surgery is an important follow-up time. Discomfort caused by strabismus operations, such as red and swollen eyes, has basically disappeared. At that time, patients can rotate the eyeball freely and complete the relevant visual function examination. Therefore, the time point chosen for this study was 1 month after the operation, and the patients in the training group began training 1 month after the operation. In addition, our inclusion and exclusion criteria are relatively strict and may exclude many patients in clinical practice, such as those with esophoria, combined with diplopia and vertical deviation, amblyopia and anisometropia. In this manner, the confounding factors in enrolled patients will be minimized, and the results will represent a powerful conclusion regarding the internal validity of this study. We have a detailed and clear therapeutic program for IXTs in the training group, including the establishment of therapeutic stages and therapeutic endpoints for each stage. This hospital-based therapy for one patient requires one orthoptic therapist to assist the training. Home-based training requires recording training logs, and computerized training would allow the real-time detection of training times and intensity. It would be helpful for us to fully capture all aspects of the therapeutic situation of each patient and analyze correlations between therapy cooperation and the actual effects of orthoptic therapy.

There are several limitations in our present study. First, the inclusion and exclusion criteria for this study are relatively strict and may not fully reflect the effect of orthoptic therapy on the exodrift of all postoperative IXTs. Second, this study uses only simple randomization, not a dynamic randomization technique based on the patient’s surgical methods, age, diopter, and other data, considering the weekly operability and our large sample. These effects will be taken into account during our data analysis.

In summary, our study will be the first large-sample, prospective randomized controlled study to confirm the effect of surgery combined with orthoptic therapy in IXTs.

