### Participant screening

Two well-trained investigators in the amblyopia and strabismus department will be responsible for the recruitment and management of participants. Those who are willing to participate and meet the eligibility criteria will be informed of the basic information related to and the requirements of the project. The inclusion and exclusion criteria are listed in Table 1.

**Table 1 Tab1:** Inclusion and exclusion criteria

Inclusion criteria	
1.	Patient is 7–17 years old.
2.	Amount of exodeviation measured using PACT at 1 month after IXT surgery meets any of the following:
	2.1 Exodeviation < 10 PD at near and distance.
	2.2 Ortho at near, and exodeviation < 10 PD at distance.
	2.3 Ortho at distance, and exodeviation < 10 PD at near.
3.	Best corrected visual acuity (BCVA) in the worse eye is 0.1 logMAR or better and there has been no previous diagnosis or treatment for amblyopia.
4.	Participant wore spectacles for at least 1 week if refractive error meets any of the following:
	4.1 Myopia< − 0.50 D and > − 6.00 D SE in either eye.
	4.2 Anisometropia < 1.50 D SER.
	4.3 No hyperopia of more than + 3.50 D SER in either eye.
5.	Refractive correction for participants meeting the above refractive error criteria must meet the following guidelines:
	5.1 For myopia, the intent is to fully correct.
	5.2 For hyperopia, the spherical component can be reduced at investigator discretion as the principal of maximum plus to maximum visual acuity.
	5.3 For astigmatism, cylinder must be within 0.25 D of full correction and axis must be within 5° of full correction.
	5.4 Myopic participants should not take any intervention for myopia control, such as orthokeratology, peripheral defocus lenses, and low-concentrate atropine.
6.	No atropine was used within the previous month.
7.	Patient had gestational age > 34 weeks and birth weight > 1500 g.
8.	Parents and participant understand protocol and are willing to accept randomization to binocular training group or sham-control group.
9.	Patient had not received prior vision training or orthoptics for any reason.
10.	The location of the home address is not very far from the hospital, and if assigned to the training group, training 1–2 times a week at hospital is acceptable.
Exclusion criteria	
1.	Coexisting vertical deviation > 5 PD.
2.	Esodeviation > 5 PD at near or distance
3.	Complaints of diplopia 1 month after surgery in the primary and reading positions.

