### Statistical analysis

Statistical analysis will be performed using SPSS software version 20.0 (IBM Corp., Armonk, NY, USA). The parameters to be calculated are the means ± standard deviations for the continuous variables and the rates (proportions) for the categorical variables.

For the primary analysis, the cumulative proportion of participants meeting the criteria for suboptimal surgical outcomes by 2 years will be compared between the 2 groups using the Kaplan-Meier method. An intergroup difference and a corresponding 95% confidence interval (CI) will also be calculated. Each of the 2 individual components of the specified suboptimal surgical outcome criteria will be assessed using the chi-square test.

For all IXTs who completed the 24-month follow-up, changes in exodeviation measured by PACT, stereoacuity, exotropia control score, accommodative amplitude and facility, and fusional convergence amplitude between baseline and the 24 months will be compared between the two groups in linear regression models that will be adjusted for the corresponding baseline values. Additionally, considering that binocular visual function is different in different age, the final data may be divided into two subgroups according to different ages.

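### The protocol promises to account for factors that simple randomisation leaves unbalanced, but the primary Kaplan-Meier comparison names no adjustment; the loss is precision, not validity

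*Protocol article*

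**What the plan says.** In the Discussion, the second limitation reads "this study uses only simple randomization, not a dynamic randomization technique". The factors it names as not balanced are "surgical methods, age, diopter, and other data, considering the weekly operability and our large sample". It closes with "These effects will be taken into account during our data analysis". It gives no model, covariate list or outcome.

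The Statistical analysis section says that the cumulative proportions with a suboptimal outcome by two years "will be compared between the 2 groups using the Kaplan-Meier method", and adds "An intergroup difference and a corresponding 95% confidence interval (CI) will also be calculated". No covariate or stratum is named for either. The continuous secondary outcomes, in children who complete 24 months, are analysed "in linear regression models that will be adjusted for the corresponding baseline values". Age appears only as an option: "the final data may be divided into two subgroups according to different ages". No cut point is given.

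**The concern.** Adjustment is specified for the secondary outcomes and left out for the primary one, where the Discussion's promise matters most. Two consequences follow.

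First, an undefined promise allows covariates to be chosen after the results are seen.

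Second, the document itself suggests that baseline status is prognostic. The Background says that key measures of binocular function may bear on long-term stability. The stereoacuity route to failure depends on baseline by arithmetic. The Primary outcome section requires a loss of two octaves or more, and Stereoacuity testing codes nil one level above the worst score. A child at the worst measurable level can therefore lose only log2(1600/800) = 1 octave on Titmus. The same holds for TNO (480 to 960) and the Distance Randot (400 to 800). On that test such a child cannot fail by this route, nor can a child already at nil. Baseline stereoacuity thus partly decides who is at risk of one of the two components.

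Age, refraction, deviation and stereoacuity are all recorded at baseline, so a better-protected analysis needs no new data collection.

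**Working it through.** **Inputs.** From Sample size: risks 16.7% and 36.5%, two-tailed alpha 0.05, 80% power, 61 per arm before and 68 after 10% dropout. From Sequence generation: simple 1:1 allocation. Not in the documents: the prognostic strength of any baseline score. It is assumed below and varied.

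**The plan's own figure.** n = [z_alpha·√(2·p̄·q̄) + 0.8416·√(p1q1 + p2q2)]² / (p1 − p2)², with p̄ = 0.266. Then √(2 × 0.266 × 0.734) = 0.6249, √(0.1391 + 0.2318) = 0.6090 and (p1 − p2)² = 0.0392.
- Two-sided: (1.96 × 0.6249 + 0.8416 × 0.6090)² / 0.0392 = 77 per arm.
- One-sided (1.645): 61 per arm.
- Two-sided power at 61 per arm: Φ[(0.198·√61 − 1.2248)/0.6090] = Φ(0.528) = 70%.

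The stated 61 is not reproduced for a two-tailed test. That is a separate point. It matters here only because 70% is the starting power.

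**Chance imbalance with 68 per arm.**
- Continuous score: the SD of the difference in means is √(2/68) = 0.1715 SD. P(imbalance above 0.25 SD, either direction) = 2Φ(−0.25/0.1715) = 14.5%.
- Binary factor with 50% prevalence: SE = √(0.25 × 2/68) = 0.0857. P(arms differ by 10 points or more) = 24%, and by 15 points or more = 8%.

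**Effect of adjusting.** 6,000 simulated trials per setting; 122 evaluable children; simple allocation; one standard-normal baseline score; logistic outcome with marginal risks of 16.7% and 36.5%. The unadjusted risk difference is compared with one standardised over the score. Simulation error on each power is about √(0.7 × 0.3/6000) = 0.6 points.

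| Assumed OR per SD | Power unadjusted | Power adjusted | Gain (points) | Variance ratio adjusted/unadjusted |
|---|---|---|---|---|
| 1.0 | 69.63% | 70.08% | 0.45 | 1.01 |
| 1.5 | 70.83% | 72.43% | 1.60 | 0.98 |
| 2.0 | 69.97% | 74.13% | 4.16 | 0.92 |
| 3.0 | 70.15% | 77.88% | 7.73 | 0.84 |

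Within simulation error, the gain at OR 3 is best read as 7 to 8 points.

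**Same simulation with no treatment effect (36.5% in both arms).** Type I error is 4.9-5.2% unadjusted and 5.0-5.6% adjusted. In the 8-9% of trials where the score is imbalanced by more than 0.25 SD in one given direction, the mean unadjusted difference is off zero by about 3, 5 and 7 points at OR 1.5, 2 and 3. The adjusted difference stays within 0.4 points of zero.

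**Model size.** Expected events are 61 × (0.167 + 0.365) = 32.5, or 68 × 0.532 = 36.2 with no dropout. At ten events per term (a rule of thumb, taken as an assumption) that supports three to four terms.

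**The case against.** The Statistical analysis section is silent on adjustment for the primary outcome; it does not exclude it. An analysis plan that is not shown may list covariates. Randomisation makes the unadjusted test valid, and its confidence interval already reflects chance imbalance. Much of this stands. The point is therefore confined to the mismatch between the two sections and to a better use of data already collected.

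A reader might also infer from Table 1, where one entry criterion is "Exodeviation < 10 PD at near and distance", that baseline deviation measures how far each child is from failing at 10 PD. The documents do not support that. Entry is judged by PACT and failure by SPCT. Ocular alignment testing says that SPCT records the manifest deviation and PACT the total. A child with 9 PD on PACT and good control may show no manifest deviation. Baseline deviation is a plausible predictor, not a distance to the threshold.

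The size of the gain rests on assumption, and zero gain lies within the range shown. The simulation used a logistic model with a standardised risk difference, not a Cox model, so it indicates scale only. The slightly higher type I error of the adjusted test could account for a small part of the gain.

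**Conclusion.** The point holds as a recommendation to improve the primary analysis. The Discussion commits to accounting for factors left unbalanced, and the primary analysis as written does not, while the secondary analyses do adjust for baseline.

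The size is modest: roughly 0, +2, +4 or +7 power points from about 70-71% at 61 per arm, for an assumed odds ratio per SD of 1, 1.5, 2 or 3. Adjustment also removes shifts of about 3 to 7 points in the minority of trials with a marked imbalance on a score that is in fact prognostic.

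Two stronger readings fail. The unadjusted comparison is neither biased on average nor invalid, since its type I error is about 5%. Nor are the baseline measures wholly unused, because the secondary regressions include the baseline value of each outcome.

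**What to change.** Before unmasking:

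- Specify the primary comparison as a Cox or discrete-time complementary log-log model. The latter suits events found only at the 6-, 12-, 18- and 24-month visits.
- Include group, baseline distance deviation (test named), baseline log stereoacuity (test named) and age as a continuous term. With group counted, this already reaches the three to four terms that the events support.
- Surgical method and refraction are named in the Discussion. Either bring one in within that limit, or state why they are left to a sensitivity analysis. Surgical method is not among the listed baseline tests, so its source must be stated. Align the Discussion sentence with the final list.
- Report the standardised 24-month risk difference with a 95% CI, for example by bootstrap. Keep the Kaplan-Meier curves and the unadjusted difference as support.
- Replace the optional two-way age split by an age-by-group interaction with continuous age in a separate secondary model. Inside the primary model, the group term would no longer test the overall effect.

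**Cost.** No new data are needed for the three covariates. The change needs a documented analysis-plan amendment and, if treated as a protocol change, the ethics submission and registry update described under Study design. The primary result would rely to some degree on a model fitted to few events, which is why the unadjusted difference should stay beside it.

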## Trial status

The trial protocol presented here has obtained approval from the Affiliated Eye Hospital of Wenzhou Medical University Review Board (2019-108-K-101) and is aligned with protocol version 2, approved on 10 August 2019. The recruitment started on 20 August 2019 and completed on 17 August 2021. Considering the importance of standardized visual function examination and orthoptic training in our study and hoping that our research can be extended and traced, we wrote this study protocol, even though recruitment has already been completed.

## Data Availability

The ethical approval does not permit to sharing the entire data that we have acquired, but the datasets used and analyzed in our study are available from the corresponding author.
